### Monitoring

2.11.

Adverse events and withdrawals will be monitored by the research team. Any adverse events and deviations will be reported to the FNRI Institutional Ethics Review Committee and included in the continuing ethics review of the trial.

## Discussion

3.

This trial aims to provide evidence to support a strategy of gene-based nutrition lifestyle intervention to manage weight loss. It will incorporate disclosure of genetic risk and recommendations based on the genetic profile of the participants.

To the best of our knowledge, this will be the first gene-based nutrition and lifestyle intervention that will adopt an intensive gene-based nutrition counseling, followed by an “inactive” period of 6 months where a “free-living” state is simulated. Along with the goals of evaluating the effectiveness of gene-based nutrition and lifestyle advice, this trial will also raise the awareness of the Filipino population regarding nutritional genomics. It acknowledges the vital role of genetic counselors in guiding the population in making informed choices upon learning their genetic risks, particularly so that all participants are carriers of at least one (or a combination) of the risk alleles for *FTO* rs9939609, *UCP1* rs1800592, and *TCF7L2* rs7903146. This trial will play an important role in leveraging a unique multidisciplinary approach to weight management that involves nutrition professionals and genetic experts.

Limitations of the study include (1) limited applicability of the findings to other populations since the trial will be conducted among overweight/obese Filipino adults only; (2) the recommendations are based only on three genetic polymorphisms, and it is likely that there are other genetic loci that may pose risks to unhealthy weight gain that will not be tackled in this study, and; (3) the intervention will only entail counseling/education and no standardized meals will be given.

## Ethics and dissemination

4.

### Research ethics approval

4.1.

This protocol was approved by the Food and Nutrition Research Institute (FNRI) Institutional Ethics Review Committee (FIERC-2021-001). In case protocol amendments are required, approval from the FIERC will be obtained before applying any changes. The current version of the protocol is version 7 (dated 2022-04-18).

### Confidentiality

4.2.

Substitute codes will be used to protect the identity of participants. A designated secured cabinet and password-protected central database will be used to store the trial documents. All recorded video conversations on Zoom will be downloaded immediately after each session and will be deleted from the Cloud once the recording is assured to have been saved in a password-protected external drive. Only the research team members who performed the randomization and allocation have access to the data collection and storage devices.

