### Study design

2.1.

The MyGeneMyDiet^®^ study is a parallel-group, single-blind, randomized controlled trial (Figure 1). Sixty-two overweight or obese adults will be recruited through waves of study enrollment. The 12-month trial will entail an “active” phase (first 6 months), followed by an “inactive” phase from months 7–12. During months 1–6, all participants will receive three sessions of nutrition counseling, including general health and information presented in nutrition modules designed for the study. A simulation of a “free-living state” will be applied to the participants during months 7–12. During this period, a follow-up data collection on month 9 and the nutrition counseling session at the end of the study on month 12 will be initiated. The inactive phase will determine whether the participants continue to adhere to the dietary and lifestyle recommendations given to them during the active phase.

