### Randomization and allocation

2.8.

All participants will be stratified by BMI using the World Health Organization (WHO) cutoff. Overweight (BMI of 25–30 kg/m^2^) and obese (BMI of >30 kg/m^2^) adults will be randomly distributed into blocks of 4, 6, and 8. Within these blocks, each participant will be randomly allocated to the intervention group (MyGeneMyDiet^®^) or control (standard weight management recommendation) using a Random Allocation Software.^1^ Two research staff will perform the randomization.

During randomization, 62 identical (31 for each treatment) sequentially numbered, opaque sealed envelopes (SNOSE) will be prepared. The sequential numbering will be synchronized with the online registration and will be used to designate participant study numbers. The randomization allocation will be concealed from the participants and the rest of the researchers involved in the month 0 visit.

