### Data collection methods

2.9.

Study outcomes will be assessed at five time points: baseline (month 0), and months 3, 6, 9, and 12. Table 2 provides an overview of data collection and outcome measures.

**Table 2 tab2:** MyGeneMyDiet^®^ study data collection and outcome measures.

Outcome measures	Active phase			Inactive phase	
	Baseline (Month 0)	Month 3	Month 6	Month 9	Month 12
Demographic information	X				
Anthropometry (weight, BMI, waist circumference, hip circumference, percent body fat)	X	X	X	X	X
Dietary intake (3-day food record)*	X	X	X	X	X
Blood chemistry analysis (glycated hemoglobin, lipid profile)	X	X	X	X	X
Physical activity level (IPAQ-SF)	X	X	X	X	X
Eating behavior (TFEQ R-18)	X	X	X	X	X
Motivation for weight loss (SP-Weight Loss)	X	X	X	X	X
Knowledge and perception of nutrigenomics	X		X		X

* Monthly 3-day food records are also collected from the participants, in addition to the food records collected on months 0, 3, 6, 9, and 12.

The research team will conduct the screening and subsequent data collection sessions at the Food and Nutrition Research Institute, Taguig City, Philippines. Pre-session visits will be conducted 2 weeks before the online nutrition counseling sessions.

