#### Dietary intake

2.9.2.

On a monthly basis, participants will be asked to complete a three-day food diary to estimate their mean energy and macronutrient intake while enrolled in the trial. The food record will consist of two non-consecutive weekdays and one weekend. In total, the participants will accomplish 12 sets of food diaries during the trial.

Proper recording of food and beverage intake and estimating food portion sizes will be explained to the participants during the orientation session. The food diary must reflect all the food and beverages consumed by the participants within the specified periods, the description of each food items (type, variety, brand name), amounts, the time of the day the meal is taken, cooking method (e.g., boiled, fried, broiled), and the source of the food (e.g., home-cooked or takeaway). A food diary form (printed or in electronic form, depending on the participant’s preference) will be distributed during the pre-session visits or approximately 2 weeks before the online follow-up sessions.

Checking and verification to ensure the completeness and correctness of the recorded intake will be done by the nutritionists of the research team, 2 weeks before the online nutrition counseling session. This will provide sufficient time for the nutritionists to analyze the dietary intake of the participants. Energy and macronutrients will be computed using the Philippine Food Composition Tables (FCT). Other foreign FCTs will be used for the items not found in the local FCT.

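### Section 4.2 gives access to the data devices only to the staff who carried out the randomisation, so data custody is joined to knowledge of the arms, and the rule does not fit the sections on data collection

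*Protocol article*

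**What the plan says.** **Access to data.** The section on confidentiality (4.2) covers substitute codes, a secured cabinet, a password-protected database and the handling of session recordings. It ends with the rule "Only the research team members who performed the randomization and allocation have access to the data collection and storage devices".

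**Who knows the arms.** Section 2.8 says "Two research staff will perform the randomization", using allocation software and sealed envelopes. It then says "The randomization allocation will be concealed from the participants and the rest of the researchers involved in the month 0 visit". Referring to the rest of the researchers sets the randomising staff apart as the ones who do know.

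**Blinding label.** Section 2.1 says "The MyGeneMyDiet^®^ study is a parallel-group, single-blind, randomized controlled trial". It does not name the blinded party.

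**Who handles data, and when.** Section 2.9 says "Study outcomes will be assessed at five time points: baseline (month 0), and months 3, 6, 9, and 12", and "The research team will conduct the screening and subsequent data collection sessions at the Food and Nutrition Research Institute, Taguig City, Philippines". For the food records, section 2.9.2 says "Checking and verification to ensure the completeness and correctness of the recorded intake will be done by the nutritionists of the research team". Section 2.9.3 has a phlebotomist draw the blood.

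**The concern.** Whoever holds the allocation list should ordinarily be kept away from the outcome data until the database is locked. Section 4.2 sets the opposite rule: knowing the allocation is what qualifies a team member for access.

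The other protections here are thin, so this matters more than it would in a fully masked trial. All participants learn their genotype at the post-test counselling session (section 2.4). Those in the intervention arm then receive advice tied to the risk alleles they carry (section 2.6.1), while controls get theirs only after month 12 (section 2.6.2). Participants may therefore work out their arm, and the dietitians must know it to counsel. Masked measurement and masked data handling are the main safeguards that remain.

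Two things are at stake. Custody by staff who know the arms touches every outcome, because queries, corrections and cleaning decisions could be made with the arm in view. Measurement is a narrower matter: waist circumference, one of the four primary outcomes, is read by tape and leaves some room for observer influence.

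**Working it through.** The point rests on the text, and the plan states no figure to reproduce. The first three steps set the sections side by side; the fourth shows what an assumed lean would do.

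**1. Who knows the arms, and who has access**

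| Question | Section | Answer |
|---|---|---|
| Who generates the allocation? | 2.8 | Two research staff |
| From whom is it concealed? | 2.8 | Participants, and the other researchers involved in the month 0 visit |
| Who has access to the devices? | 4.2 | Only those who performed randomisation and allocation |

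The group in the third row is the group left out of the second. Allocation knowledge and data custody therefore coincide.

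**2. Does the rule fit the data-collection sections?** Section 2.9 has the research team run the sessions, section 2.9.2 has nutritionists check and analyse the food records, and section 2.9.3 has a phlebotomist take blood. If access were literally confined to the randomising staff, the nutritionists could not do their work unless they were the same people. Either the word *only* is wrong, or the rule was meant for something narrower. The sections conflict on a literal reading.

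**3. How far does stated concealment reach?** There are five assessment points: months 0, 3, 6, 9 and 12. The one sentence that conceals allocation from researchers refers to those involved at month 0. All post-baseline primary data come from the other 5 − 1 = 4 visits. If month 0 names a set of people, those people may stay masked later, but the sentence does not tie them to the later measurements.

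**4. Illustration of size (the lean is an assumption)**

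Inputs: n = 26 per arm (section 2.5), two-sided alpha 0.05 and a two-sample t-test (section 2.10). Assumed: no true effect, and a systematic lean of d standard deviations in one arm.

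Formula: noncentrality = d × √(n/2), with √(26/2) = 3.606; degrees of freedom = 2 × 26 − 2 = 50; critical value 2.009. The false-positive rate is the probability that a noncentral t exceeds the critical value in absolute size.

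| Assumed lean d | Noncentrality | False-positive rate |
|---|---|---|
| 0 | 0 | 0.050 |
| 0.1 SD | 0.361 | 0.064 |
| 0.2 SD | 0.721 | 0.109 |
| 0.3 SD | 1.082 | 0.186 |

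With all 31 per arm retained, the 0.2 SD case gives 0.121. For scale, if the SD of change in waist were 5 cm (an assumption), 0.2 SD would be 0.2 × 5 = 1 cm.

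**The case against.** The strongest reply is that the access rule is a confidentiality statement. It follows directly on the sentence about moving recordings to an external drive and may have been meant to restrict custody of recordings and storage media. It does not say who measures, enters, cleans or analyses outcomes. A reader might infer that two unblinded people will measure, enter or alter the outcome data. The documents do not support that, and sections 2.9 to 2.9.3 point the other way. This part of the objection stands.

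A reader might also infer that concealment lapses after month 0. That is only one reading of section 2.8. The phrase may identify a group of researchers rather than set an end date, and concealment from participants carries no stated limit. This stands too. Rosters and masking procedures may be in the full protocol (section 4.1 cites version 7), so the article's silence on them is not counted here.

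The routes to bias are also limited. Weight and body fat come from an analyser and BMI is calculated. For waist, section 2.9.1 fixes duplicate readings, a third reading when they differ by more than 0.5 cm, and the average of all readings, so the repeat is not discretionary. Intention-to-treat analysis (section 2.10) limits arm-aware exclusions.

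What the objection does not remove is the sentence itself. Condensing a protocol into an article can explain missing detail. It does not explain an explicit rule that names the data collection devices as well as the storage devices and gives access to the staff who hold the allocation.

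**Conclusion.** The point holds in a limited form. As written, section 4.2 joins data custody to knowledge of the arms, and it cannot be literally reconciled with sections 2.9 to 2.9.3. That the randomising staff know the allocation is an inference from the wording of section 2.8, but a direct one.

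The documents do not show that bias will occur. The measurement risk is mainly for waist; the custody risk extends to all outcomes. It would be tempting to say that the false-positive rate is about 11%. That figure depends wholly on an assumed lean of 0.2 SD. With 26 per arm, the rate is about 6% at 0.1 SD and 19% at 0.3 SD, and nothing in the documents favours one of these. It should not be carried over to scale weight, on which the sample size is based. The change is worth making because it closes an avoidable route to bias at little cost.

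**What to change.** - **Section 4.2:** reverse the rule. Staff who hold the allocation list have no access to outcome data or devices until database lock. Existing team members who do not know the arms hold, enter and clean the data.
- **Section 2.8:** name who is blinded, and state that concealment applies to anthropometry and data-entry staff at months 3, 6, 9 and 12 as well as month 0. Dietitians who counsel participants do not take the anthropometric measurements.
- **Sections 2.8, 2.9, 2.9.2 and 4.2:** reconcile them so that each task (randomising, counselling, measuring, checking food records, holding the database) has a stated role and a stated level of access.

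The cost is a few sentences, a reassignment of roles within the present team and slightly tighter rostering at visits. No extra participants or visits are needed. Section 4.1 requires ethics committee approval before the change is applied. If follow-up has already begun, masked entry and cleaning before lock can still be adopted.

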### Dissemination policy

4.3.

The research findings will be submitted to and published in peer-reviewed journals.

## Data availability statement

The original contributions presented in the study are included in the article/Supplementary material, further inquiries can be directed to the corresponding author.

## Ethics statement

The studies involving human participants were reviewed and approved by the FNRI Institutional Ethics Review Committee (FIERC-2021-001). The participants provided their written informed consent to participate in this study.

